#### ● Histopathology

Rationale: Endoscopy will be performed for the sole purpose of obtaining biopsy specimens at baseline, following single exposure, and following one week of QD exposure. Samples will be obtained at each flexible sigmoidoscopy and set aside for batch sectioning and H&E staining. Slides will be reviewed and scored by a qualified pathologist using the qualitative scoring system (see Appendix III) developed for the HPTN 056 study and adapted from validated scoring systems used in inflammatory bowel disease (IBD).

This scoring system is intended to improve upon the coarse scoring system used in past studies. Prior to the HPTN 056 study, one rectal microbicide study using histological data, employed a simple scoring system of normal, slightly abnormal, or abnormal. Using this histological system 69% of the placebo recipients and 89% of the N-9 recipients had slightly abnormal or abnormal rectal biopsies. The scoring system developed for the HPTN 056 study might provide better discrimination between abnormal and normal histology.

These indices are research measures only and will not be available or used in real-time to make clinical decisions, but will be analyzed as a secondary endpoint. In the immunologically responsive rectum, histologic assessment alone may be inadequate to evaluate subclinical cellular alterations in mucosal integrity. However, histology will inform in part the safety profile of the study products.

Histology is preferable to visual inspection which is a coarse measurement of mucosal health for several reasons 1) the wide spectrum of normal mucosal appearance, 2) inter-observer variability, 3) intra-observer variability. The single-cell rectal lining is easily damaged and quickly repairs. Presence of epithelial cells in effluent is normal; mucosal redness, flushing, loss of vascular pattern and even small erosions may all be normal variants and/or a result of colonic preparations. Should any significant abnormalities be noted during the exam, they will be recorded as adverse experiences (see Appendix IV and V Toxicity Tables), but endoscopic appearance will not be a study endpoint.

- Microflora

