## 2.2 Study Design

This is a phase I randomized, blinded, placebo-controlled study of the safety and acceptability of the vaginal formulation of UC-781 gel, when administered rectally, to be conducted in 36 adults (12 per group) residing in the Los Angeles, CA area. All of the participants will be HIV negative. The study design is summarized in the Schema above and the Schedule of Events in Appendix I.

This study will involve 2 stages of treatment. Each treatment stage is independent of the other. **This study aims to examine the effects of 2 different dosing regimens, NOT cumulative toxicity over both stages.** Participants will undergo extensive evaluation during 5 study visits over an approximately 7-14 week period. In addition, acceptability assessments will be completed at baseline and Visit 5.

Interested participants will enter a screening period, which includes (Visit 1) and if necessary a medication washout period. Subjects, who are deemed eligible after this screening period, will return for a baseline evaluation (Visit 2), including clinical evaluation and mucosal specimen collection, as well as a baseline behavioral assessment (BBQ). The BBQ questionnaire will be administered by CASI. Subjects may complete the web-based CASI in the privacy of their own home. If a subject does not have access to the internet, prefers to complete the BBQ at the study site, or requires assistance in using the CASI, they will be accommodated at the study site.

After completing Visits 1 and 2, eligible subjects will be randomized to one of three groups: 0.1% UC-781 gel, 0.25% UC-781 gel, or a placebo gel (12 per group). A subset of 9 subjects (3 from each group) will also participate in a pK sub-study, which will include 6 timepoints (Visit 3- pre, 0.25 hr, 2 hr, 4 hr, Visit 3A- 24 hr, and Visit 5- 1 day post-QD dose draw). During randomization, study staff will be notified if the participant is randomized to the pK sub-study. Subjects will be randomized in blocks of 3, one per group to minimize imbalance in treatment assignments. The first three subjects enrolled in each of three treatment groups will be selected for the pK sub-study. It is possible that participants may refuse to participate in the sub-study, and spots will continue to be offered as needed.

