The basic model for analyzing continuous measures adjusting for baseline differences will be the analysis of covariance (ANCOVA) model regressing the continuous parameter at either post-Treatment 1 or post-Treatment 2 on the continuous baseline value and the categorical treatment group membership (with placebo as the reference group). The estimated regression coefficients for the treatment group will then be directly interpretable as the difference between low vs. placebo and high vs. placebo, post-Treatment 1 or post-Treatment 2 after adjusting for baseline differences. This model without the baseline values reduces to the simple one-way ANOVA model with treatment group as the predictor. For analyzing binary or ordinal measures, we will use the logistic regression version of these models. That is, we will regress the outcome post-Treatment 1 or post-Treatment 2 on group membership and on baseline value (when adjusting for baseline differences).

As we will be analyzing group differences in a large number of parameters, some attempt must be made to account for multiple hypothesis testing. We will address this multiple comparisons problem both informally and formally. Informally, particular group differences significant at the 0.05 level or smaller will be flagged as at least suggestive and those with extremely strong p-values (e.g. 0.001 or less) will be carefully examined. In addition, differences seen consistently for related parameters will carry more weight. Formally, we will apply corrections to the p-values. Of these, the Bonferroni method is the simplest, but also the weakest. We will employ the more powerful stepdown methods implemented in

the MULTTEST procedure in SAS v 9.1 (SAS Institute, Cary, NC).

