We will also investigate longitudinal (three or four time points) and/or multivariate (simultaneous examination of multiple measures in a set) modeling techniques. The longitudinal analyses will most likely not be additionally informative, as there are only three time points for most of the parameters. Multivariate techniques are expected to result in potentially substantial power increases. Our previous studies with phenotype and cytokine panels have shown strong correlations between measures as well as good stability over time (i.e. high intrasubject correlations) in steady state for many of the measures. In this setting, for example, factors derived using principal components analysis would likely have stronger association with group membership than any one particular measure in the set. An additional strength of the longitudinal and multivariate approaches is that they provide an alternative solution to the multiple testing problem that arises with examining each timepoint and each parameter individually.

- Epithelial Sloughing

The simplest analysis for the epithelial sloughing measurements will look at the presence or absence of sloughing. Additionally, we may employ the five point ordinal scale of, which ranges from 0 (no evidence of sloughing) up to 4 (evidence in all four quadrants). For these data, there is baseline measurement will allow screening out of post-Treatment 1 false positives.

- Histopathology

As in the sloughing data, we will begin by examination of a two point (normal versus abnormal) or three point (normal, slightly abnormal, abnormal) scales. Based on initial analyses of the HPTN 056 histopathology panel data, we do not expect that quantitative measures will be substantially more informative than simple qualitative readings.

- Mucosal mononuclear cell phenotype

Many of the flow cytometry measurements from the HPTN 056 study are quite stable across time. Parameters with high intrasubject correlations (RFI measures are log-transformed) include %CD3, %CD4, %CD8, %CD31, CD38RFI on CD4+, CD38RFI on CD8+, %CD38|CD4, and %CD38|CD8 which have intrasubject correlations of between 0.7 and 0.9. Thus, we expect that clinically important differences in these parameters between treatment groups would be found to be statistically significant in our analyses. CCR5-related parameters had moderate stability (intrasubject correlations of around 0.5).

- Mucosal cytokine Profile

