## **7.7 Statistical Procedures for Microflora Studies**

Microflora measures will be graded on a 0 to 4 ordinal scale and recorded at baseline and post-exposure. Depending on the empirical distributions across the points in this scale, statistical procedures will either involve analysis of the actual pre-post differences (ordinal) or dichotomized versions of the pre and post scores (binary). In the ordinal case, we will use one sample and multi-sample signed rank tests to examine whether (1) there is an overall change in microflora levels and (2) whether the treatment groups differ significantly from each other in pre-post change. Similarly, if dichotomization is more appropriate, then the binary baseline and post-exposure data will be analyzed using exact McNemar tests (to examine if levels change significantly pre to post) and Fisher tests (to examine whether the pre and post prevalence levels differ between groups).

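### Section 7.6 makes no provision for an arm at 0/12 or 12/12 in its logistic models, where the usual coefficient test gives p near 1 even for a large difference

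*Protocol*

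**What the plan says.** Section 2.2 sets the size: the study is "to be conducted in 36 adults (12 per group) residing in the Los Angeles, CA area". Section 7.6 first describes an ANCOVA for continuous mucosal measures, with placebo as the reference group, and says of it: "The estimated regression coefficients for the treatment group will then be directly interpretable as the difference between low vs. placebo and high vs. placebo". It then carries the structure over: "For analyzing binary or ordinal measures, we will use the logistic regression version of these models". Every analysis is to be run both with and without the baseline value.

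The binary outcomes covered include sloughing ("The simplest analysis for the epithelial sloughing measurements will look at the presence or absence of sloughing") and histology, which starts from a two- or three-point scale. Section 7.6 names no test statistic for the logistic models and does not mention empty cells.

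Section 7.7 handles the same kind of data differently. If the microflora scores are dichotomised, "the binary baseline and post-exposure data will be analyzed using exact McNemar tests", with Fisher tests for the comparison between groups.

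**The concern.** With 12 per arm, a binary outcome can easily be absent from a whole arm or present in all of it. The likelihood then has no finite maximum in the treatment coefficient: the estimate drifts upward until the software stops, and its standard error grows much faster. A Wald p-value computed from the two is close to 1 however large the observed difference. Adding a baseline term divides the cells further.

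The question in 7.6 is whether either UC-781 arm shows more damage than placebo. A clean placebo arm beside a damaged active arm is the clearest answer the data could give, and it is the pattern in which this test fails. Such a result would miss the 0.05 flag in 7.6, and no stepdown adjustment lowers a raw p-value near 1.

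**Working it through.** **The plan's own figures.** Section 7.4 gives the chance of at least one event among 12 participants. At a true rate of 20% it is 1 − 0.80^12 = 93.1% (stated as more than 90%). At 1% it is 1 − 0.99^12 = 11.4% (stated as 11%). Both reproduce. No operating characteristic is given for sloughing or histology.

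**Inputs.** 12 per arm (2.2); placebo as reference (7.6); 0.05 flag (7.6), taken as two-sided because sidedness is not stated. Sloughing rates are assumptions, shown as a range.

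**One separated table: placebo 0/12, UC-781 6/12.** With no baseline term the three-arm model is saturated, so each contrast depends only on its own two arms, apart from numerical drift.

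- Wald, maximum likelihood: at a usual convergence tolerance the coefficient is 22.2 and its standard error about 19,130. So z = 22.2/19,130 = 0.0012 and p ≈ 0.999. Both values depend on when the iterations stop. The p-value is also about 0.999 at every other UC-781 count tried between 3/12 and 10/12.
- Fisher, two-sided: 2 × C(12,6)/C(24,6) = 2 × 924/134,596 = 0.0137.
- Likelihood ratio: G = 2[12 ln 0.5 − (6 ln 0.25 + 18 ln 0.75)] = 2[−8.318 + 13.496] = 10.36 on 1 df, p = 0.0013.
- Firth: in this saturated model the penalty acts like adding 0.5 to each cell. The coefficient is ln(6.5/6.5) − ln(0.5/12.5) = 3.22, which is finite; penalised likelihood-ratio p = 0.0046.

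**One placebo event more: 1/12 against 6/12.** The coefficient is ln(6/6) − ln(1/11) = 2.40, with SE = √(1/1 + 1/11 + 1/6 + 1/6) = 1.19. So z = 2.01 and p = 0.045. A cleaner placebo arm therefore moves the Wald p-value from 0.045 to about 1.

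**How often separation occurs.** P(placebo 0/12) = (1 − p)^12:

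| Assumed true placebo rate | P(0/12) |
|---|---|
| 1% | 89% |
| 5% | 54% |
| 10% | 28% |
| 20% | 7% |

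Histology can separate at the other end. Section 2.1.2 reports, from an earlier study of another product: "Using this histological system 69% of the placebo recipients and 89% of the N-9 recipients had slightly abnormal or abnormal rectal biopsies". Giving the placebo arm the first rate and both UC-781 arms the second, the chance that some arm is 12/12 is 1 − (1 − 0.69^12)(1 − 0.89^12)² = 1 − 0.988 × 0.753² = 44%.

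**Power.** This is the sum, over all 13 × 13 outcomes, of P(a)·P(c) where p ≤ 0.05, with 12 against 12 and separated tables counted as non-significant for Wald:

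| True rates | Wald | Fisher | Firth | Likelihood ratio |
|---|---|---|---|---|
| 5% vs 50% | 25% | 59% | 75% | 78% |
| 2% vs 50% | 13% | 71% | 85% | 90% |
| 20% vs 60% | 50% | 39% | 57% | 57% |
| 69% vs 89% | 6% | 9.5% | 20% | 25% |

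**Size.** The same sum with equal rates in both arms gives, for Firth, 0.2% at 5%, 3.9% at 20%, 6.4% at 50% and 5.0% at 69%. For the likelihood ratio it gives 2.1%, 7.1%, 6.4% and 5.6% at the same rates.

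**The case against.** Four objections have force.

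1. **The plan does not name the Wald test.** A reader might infer that ordinary logistic regression as such breaks down. The documents do not support that. On the same model the likelihood-ratio test gives p = 0.001 at 0/12 against 6/12, and its power is at least that of Firth. The sentence about reading coefficients was written for the ANCOVA, so carrying it over to Wald tests is an inference. The choice of test may also stand in an analysis plan that is not shown. This limits the point to an unguarded default. The infinite odds ratio remains whichever test is used.

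2. **Nothing says sloughing is rare on placebo.** Section 2.1.2 calls some epithelial cells in the effluent normal. Section 7.6 expects the baseline measurement to screen out false positives, which would push the placebo count down, but by an unknown amount. Placebo 0/12 is therefore a possibility to plan for, not an expected result.

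3. **Fisher's test is no general remedy.** At 20% against 60% it has 39% power against 50% for Wald. It should not be the main replacement.

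4. **These are secondary endpoints.** Section 1.1 says the assays will not be safety indices. Section 7.6 also gives weight to consistency across related parameters, and 0/12 against 6/12 would be plain in any table. This limits the consequence, but a reported p near 1 beside such counts would still mislead.

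**Conclusion.** The point holds as a gap in 7.6: logistic regression is fixed for binary and ordinal measures at 12 per arm, with nothing said about an empty or full arm. If that occurs and the usual coefficient test is reported, a difference of 0/12 against 6/12 comes out at p ≈ 0.999 instead of 0.001 to 0.014. The loss of power, 25% against 75% for Firth at 5% versus 50%, rests on assumed rates. It shrinks as the placebo rate rises (50% against 57% at 20% versus 60%).

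Two further readings are tempting and are not supported:

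- **Underpowered histology as an error in the plan.** Power at 69% against 89% is low under every test, between 6% and 25%. That is a sample-size limit which the choice of test does not cure. The protocol claims detectability for at least four of six parameter sets without naming them, so it promises nothing specific for histology. The two rates also come from another product on an older scale.
- **Ordinal scores must come before dichotomised ones.** Section 7.6 already allows a five-point sloughing scale and only begins with coarse histology. The order is a preference.

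**What to change.** Add to 7.6: binary and ordinal mucosal outcomes, with and without baseline adjustment, will be analysed by Firth-penalised logistic regression (in proportional-odds form for ordinal outcomes), with penalised likelihood-ratio p-values and profile penalised-likelihood confidence intervals; Wald tests and intervals will not be used. Fisher's exact test may be reported as a supportive unadjusted check, with a note that it is conservative at moderate placebo rates.

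Firth is preferred to the plain likelihood-ratio test because it also gives a finite odds ratio when an arm is 0/12 or 12/12. Section 7.7 already accepts small-sample methods for binary data, so the principle is not new to the protocol.

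The cost is a sentence or two of text and slightly more analysis work, including a check that the software release in use offers the penalised fit. No change to data collection or sample size is needed.

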#### PRN visits

- Any complications that arise may require further clinical evaluation.

**Study Population:** HIV negative men and women with a history of RAI \*

*\*Refers to coitus only, does not include manual stimulation or the use of sex toys or purgatives.*

**Study Size:** A total of 36 participants (12 per treatment group).  
A subset of 9 participants will be assigned to the pK study.

|                           |                                                |            |
|---------------------------|------------------------------------------------|------------|
| Treatment Regimen: | Treatment Stage 1- Study gel administered once | Clinic     |
|                           | Full 7-day recovery period                     |            |
|                           | Up to 3 weeks later:                    |            |
|                           | Treatment Stage 2- Study gel QD x 7 days       | Outpatient |

**Study Duration:** Participant accrual will take approximately 9-12 months and each participant will be on study for approximately 7-14 weeks. The total duration of the study will be approximately 18 months. Specimen and data analysis will require an additional four months.

**Primary Objective:** To evaluate the safety and acceptability of 0.1% and 0.25% UC-781 vaginal microbicide gel versus placebo when applied rectally.

Parameters to be studied include: Frequency of  $\geq$  Grade 2 adverse events  
Acceptability assessments

**Secondary Objective:** To determine whether use of study product is associated with rectal mucosal damage characterized by the following:

Parameters to be studied include: Epithelial sloughing  
Histopathology  
Microflora  
Mucosal mononuclear cell phenotype  
Mucosal cytokine profile  
Mucosal immunoglobulins  
Fecal calprotectin  
Explants- Mucosal cytokine profile and susceptibility to HIV infection

**Tertiary Objective:** To determine the pharmacokinetics of UC-781 vaginal microbicide gel administered rectally in a subset of participants.

Parameters to be studied include:  
UC-781 blood levels to determine absorption from the GI tract

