### 2.1.2 Secondary Objective

To determine whether use of study product is associated with rectal mucosal damage characterized by the following:

Parameters to be studied include:

- Epithelial Sloughing

Rationale: The sloughing assay is integral to the evaluation of microbicides in the rectum. The only microbicide previously studied in the rectum, is N-9, which led to rapid exfoliation of the rectal epithelium in mice and variable abnormality in humans. A recent study has demonstrated that up to 41% of men who have sex with men (MSM) use vaginal products containing spermicides for lubrication during rectal sex. It is important to have confidence that any microbicide going to market will not have a similar effect.

Using the N-9 example, it is expected that evidence of any injury may be apparent within 15 minutes of exposure to an offending agent. In the case of N-9, substantial reconstitution of these changes occurred by 2 hours and microscopically normal

epithelium was noted after 24 hours. The observation of epithelial sloughing was made by performing a rectal lavage and examining the effluent for epithelial cells. Measurements were conducted using either microscopy, looking for sheets of epithelia, or by counting the cells with a Coulter Counter.

Given the above information, it is best to obtain lavage specimens within the 15 minute –2 hour window after application of a product rectally. Therefore, in this study the first treatment stage will include rectal lavage in order to monitor subjects for epithelial sloughing. Although presence of some epithelial cells in effluent is normal, a dramatic increase from baseline would be concerning. In order to avoid the confounding effects of the standard pre-sigmoidoscopy prep (a hypertonic enema), a Normosol-R pH7.4 (See Appendix XI for package insert) enema will be used instead. Rectal lavage will be performed during the endoscopy at approximately 5 cm. Careful attention will be paid to perform the second lavage at 5 cm to decrease the likelihood of washing the UC-781 off of the mucosa at biopsy sites further up the colon and avoid confounding results caused by a the small amount of KY-like lubricant routinely used during the endoscopy procedure.

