## **7.6 Statistical Procedures for Analysis of Mucosal Damage Parameters**

The associations of six sets of mucosal parameters with the use of study product will be examined as a secondary objective. Four of these parameter sets (Histopathology, Cell Phenotype, Cytokine profile, Fecal Calprotectin) are collected three times per patient: at baseline, post-Treatment 1 and post-Treatment 2. The remaining two sets (Epithelial Sloughing and Immunoglobulins) are four times per patient: at baseline, pre- and post-Treatment 1, and post-Treatment 2. For all six parameter panels, the main question of interest is whether the three treatment groups (placebo, low, and high) have systematically different mucosal damage parameters post-Treatment 1 and post-Treatment 2. In particular, we will be assessing whether either of the UC-781 treatment groups have evidence of more mucosal damage than the placebo group. As described below, at least four of the six parameter sets should be stable and sensitive enough that important clinical differences would be statistically detectable.

As subjects will be randomized to the three treatment groups, systematic baseline differences are not expected; however, due to the relatively small study size, it is quite likely that many parameters will be quite different between treatment groups at baseline. All analyses will therefore be conducted both with and without controlling for baseline measurements. For continuous measures, it is well-known that controlling for baseline differences in regression models is more powerful than analyzing changes from baseline.

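### The committed sloughing analysis in Section 7.6 is yes/no, so it cannot show the rise from baseline that Section 2.1.2 calls concerning, and the undefined baseline screen may hide it further

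*Protocol*

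**What the plan says.** Section 7.6 (Epithelial Sloughing) opens with a binary outcome: "The simplest analysis for the epithelial sloughing measurements will look at the presence or absence of sloughing". The graded measure is permitted rather than planned: "Additionally, we may employ the five point ordinal scale of" two cited studies, running from 0 for no evidence to 4 for evidence in all four quadrants. It then says: "For these data, there is baseline measurement will allow screening out of post-Treatment 1 false positives".

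The general part of Section 7.6 also applies. "All analyses will therefore be conducted both with and without controlling for baseline measurements". "For analyzing binary or ordinal measures, we will use the logistic regression version of these models", with treatment group and, when adjusting, the baseline value as predictors.

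Section 2.1.2 describes the signal of harm. Under Epithelial Sloughing: "Although presence of some epithelial cells in effluent is normal, a dramatic increase from baseline would be concerning". Under Histopathology: "Presence of epithelial cells in effluent is normal".

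Although the opening of Section 7.6 mentions a sample before Treatment 1, Section 5.3.2 schedules only one Visit 3 lavage, after the gel. The baseline for Treatment 1 is therefore the Visit 2 lavage, nominally one to three weeks earlier.

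**The concern.** Section 2.1.2 treats harm as a matter of degree: some cells are expected, and a large increase is the warning. Section 7.6 commits to an outcome without degree. It sets no threshold for presence, and scale point 0 means no evidence at all, so a small normal finding may already count as positive.

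A participant with slight sloughing at Visit 2 and heavy sloughing about 30 minutes after the gel shows the pattern that Section 2.1.2 singles out. On the yes/no score that participant is positive both times. A screen that treats baseline positives as grounds for calling a later positive false could apply to exactly this person.

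At stake is the ability of this assay to detect a real effect. Section 2.1.2 regards the assay as central to evaluating rectal microbicides because of the experience with nonoxynol-9.

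**Working it through.** The protocol gives no sloughing rate, power or sample-size figure, so there is nothing to reproduce. The check has three steps.

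**1. Coding.** Let the Visit 2 and Visit 3 scores be s0 and s1, and let y = 1 if the score is above 0.

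| Participant | s0 → s1 | y0 → y1 |
|---|---|---|
| A, sharp rise | 1 → 4 | 1 → 1 |
| B, no change | 1 → 1 | 1 → 1 |

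Within a treatment group, A and B give the logistic model the same outcome and the same baseline value. Neither the adjusted nor the unadjusted model can tell them apart. The 0–4 score can (4 against 1).

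**2. Exact calculation.** Arm size is from the Schema: "A total of 36 participants (12 per treatment group"). Everything else is assumed: a true rise in r = 60% on gel and 10% on placebo, independent of baseline; a share q positive at baseline, all of whom stay positive; two-sided Fisher test at 0.05, one gel arm against placebo.

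- Increase from baseline, all 12 kept: probability r.
- Present/absent, unscreened: q + (1 − q)r. At q = 0.5 this is 0.5 + 0.5 × 0.6 = 0.80 against 0.5 + 0.5 × 0.1 = 0.55.
- Baseline positives recoded as negative: (1 − q)r. At q = 0.5 this is 0.30 against 0.05.
- Baseline positives excluded: probability r in 12(1 − q) per arm.
- True rises in a gel arm: 12 × 0.6 = 7.2 expected, of which 7.2q are in baseline positives.

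| q | Increase from baseline | Present/absent | Recoded | Excluded (n per arm) | Rises in baseline positives |
|---|---|---|---|---|---|
| 0 | 0.64 | 0.64 | 0.64 | 0.64 (12) | 0 |
| 25% | 0.64 | 0.34 | 0.39 | 0.49 (9) | 1.8 |
| 50% | 0.64 | 0.14 | 0.16 | 0.14 (6) | 3.6 |
| 75% | 0.64 | 0.04 | 0.02 | 0 (3) | 5.4 |

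**3. Simulation with the graded score.** Assumptions: 12 per arm; score 3–4 in 60% of gel users and in no placebo user; background score 1 at the rate shown, with within-person persistence 0.5. Fisher's test is used for the binary outcomes and the Mann-Whitney test for the 0–4 score.

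| Background | Present/absent | Recoded | Excluded | Rank test, 0–4 score |
|---|---|---|---|---|
| 0 | 95% | 95% | 95% | 99% |
| 25% | 48% | 42% | 53% | 84% |
| 50% | 20% | 11% | 20% | 80% |
| 75% | 5% | 1% | 3% | 83% |

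At 50% background, dichotomising costs 80 − 20 = 60 points. Screening then costs a further 20 − 11 = 9 points if positives are recoded and none if they are excluded. At 25%, dichotomising costs 84 − 48 = 36 points; recoding costs 6 more, while exclusion gains 5.

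A rank test on the change from baseline gave about 84–87% over the same backgrounds. With 40% toxicity and 50% background, power was about 10% for present/absent, 5% with recoding and 45% for the rank test on the score. The graded figures come from an unadjusted rank test, not from the ordinal logistic model, so they are indicative.

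**The case against.** A reader might infer that the protocol discards a participant who was positive at baseline and worsened. It does not say so. The sentence is garbled, and screening could mean exclusion, recoding or adjustment. It also directly follows the 0–4 scale, and on that scale a comparison with baseline could preserve the rise. This objection stands: discarding is one possible reading, not a stated rule.

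A reader might also infer that screening biases the comparison towards no damage. That is not established. The Visit 2 lavage precedes randomisation, so excluding on it leaves the arms comparable and costs participants. In the tables, screening sometimes does no worse than leaving it out.

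Section 7.6 already plans models with and without baseline, which keep every participant in at least one analysis. That is true, but with a binary outcome the rise stays invisible in both.

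Sloughing may mean epithelial sheets rather than loose cells. Section 2.1.2 mentions microscopy for sheets as well as cell counting. If only sheets count, background may be low and the loss small or nil. This limits the size. However, Section 7.6 sets no such threshold, and the remark about normal cells stands in the rationale for this very assay.

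Finally, Section 1.1 calls these assays developmental and makes them secondary endpoints rather than safety indices, and an SAP might firm up the scale. The first point lowers the severity. On the second, the difficulty is the order of commitment that the protocol itself states. Section 7.7, by contrast, commits microflora to a 0–4 grade from the outset.

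**Conclusion.** The concern holds in limited form. The only firmly planned sloughing outcome cannot register the change that Section 2.1.2 identifies as concerning, and the screening sentence is undefined in a way that could apply to the same participants. The main fault is dichotomising. The effect of screening depends on how it is done and is nil if nobody has sloughing at baseline.

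With 60% toxicity on gel and 25–75% background, power is about 48% falling to 5% for present/absent, against about 80–85% for the graded score. Both rates are assumptions, since the protocol gives neither. At zero background the two approaches are close (95% and 99%).

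The documents do not support saying that participants are discarded or that the result is necessarily biased towards safety. Severity is moderate: this is a secondary endpoint, and the primary safety measure is adverse events of Grade 2 or higher.

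**What to change.** Rewrite the Epithelial Sloughing paragraph of Section 7.6 before unblinding:

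- Make the 0–4 score the planned sloughing outcome, in all randomised participants with a lavage, whatever their Visit 2 result.
- Analyse it with the ordinal logistic model already in Section 7.6, with the Visit 2 score as covariate, or by the rank of the change from Visit 2. Name one of the two in advance.
- Delete the sentence on screening out false positives.
- Keep present/absent as a descriptive table.

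The cost is one paragraph. Lavages are already collected at Visits 2 and 3, and the scale is already named. The downside is that each lavage must be graded rather than marked yes or no.
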